## Abstract

**Background:**

Sacral neuromodulation has become a well-established and widely accepted treatment for refractory non-neurogenic lower urinary tract dysfunction, but its value in patients with a neurological cause is unclear. Although there is evidence indicating that sacral neuromodulation may be effective and safe for treating neurogenic lower urinary tract dysfunction, the number of investigated patients is low and there is a lack of randomized controlled trials.

**Methods and design:**

This study is a prospective, randomized, placebo-controlled, double-blind multicenter trial including 4 sacral neuromodulation referral centers in Switzerland. Patients with refractory neurogenic lower urinary tract dysfunction are enrolled. After minimally invasive bilateral tined lead placement into the sacral foramina S3 and/or S4, patients undergo prolonged sacral neuromodulation testing for 3–6 weeks. In case of successful (defined as improvement of at least 50% in key bladder diary variables (i.e. number of voids and/or number of leakages, post void residual) compared to baseline values) prolonged sacral neuromodulation testing, the neuromodulator is implanted in the upper buttock. After a 2 months post-implantation phase when the neuromodulator is turned ON to optimize the effectiveness of neuromodulation using sub-sensory threshold stimulation, the patients are randomized in a 1:1 allocation in sacral neuromodulation ON or OFF. At the end of the 2 months double-blind sacral neuromodulation phase, the patients have a neuro-urological re-evaluation, unblinding takes place, and the neuromodulator is turned ON in all patients. The primary outcome measure is success of sacral neuromodulation, secondary outcome measures are adverse events, urodynamic parameters, questionnaires, and costs of sacral neuromodulation.

**Discussion:**

It is of utmost importance to know whether the minimally invasive and completely reversible sacral neuromodulation would be a valuable treatment option for patients with refractory neurogenic lower urinary tract dysfunction. If this type of treatment is effective in the neurological population, it would revolutionize the management of neurogenic lower urinary tract dysfunction.

**Trial registration:**

*Trial registration number:*http://www.clinicaltrials.gov; Identifier:
NCT02165774.

## Background

Neurogenic lower urinary tract dysfunction (LUTD) is highly prevalent and affects the lives of millions of people worldwide. It has a major impact on quality of life and, besides the debilitating manifestations for patients, it also imposes a substantial economic burden for every healthcare system. Neurogenic LUTD is a challenge because all available treatment modalities (i.e. conservative, minimally invasive and surgical therapies) may either fail or be invasive causing considerable complications and/or side effects.

Sacral neuromodulation (SNM)
[1] has become a well-established and widely accepted treatment for patients with refractory LUTD such as non-obstructive chronic urinary retention, urgency frequency syndrome, and urgency incontinence
[2-6] and it has been incorporated into the guidelines of the European Association of Urology (EAU) (
http://www.uroweb.org), the International Consultation on Incontinence (ICI)
[7], and the National Institute for Health and Clinical Excellence (NICE) (
http://www.nice.org.uk). Originally, SNM was not considered an option for neurogenic LUTD but some studies suggested that it is also effective in neurological patients
[3,8]. Considering that SNM is minimally invasive and completely reversible, it is of great interest whether this is a valuable treatment option for patients with neurogenic LUTD. In a recent systematic review and meta-analysis
[9], we found that there is evidence indicating that SNM may be effective and safe for the treatment of this group of patients. However, the number of investigated patients is low with high between-study heterogeneity and there is a lack of randomized controlled trials
[9].

We therefore designed a prospective, randomized, placebo-controlled, double-blind multicenter clinical trial to assess the efficacy and safety of SNM for treating patients with neurogenic LUTD. The study hypothesis is that in patients with refractory neurogenic LUTD, SNM leads to an at least 35% increase in success rate as compared to placebo (i.e. sham) stimulation within 2 months, i.e. SNM is considerably more effective than placebo (i.e. sham) stimulation.

## Methods and design

### Study design

This study is a prospective, randomized, placebo-controlled, double-blind multicenter trial including 4 SNM referral centers in Switzerland: Neuro-Urology, Spinal Cord Injury Center & Research, University of Zürich, Balgrist University Hospital, Zürich; Department of Urology, Cantonal Hospital St. Gallen, St. Gallen; Neuro-Urology, Swiss Paraplegic Center Nottwil, Nottwil; Department of Urology, University of Bern, Bern.

In case of successful prolonged SNM, the neuromodulator is implanted and patients are randomized using a computer program considering 3 strata according to the neuro-urological diagnosis, i.e. a) urgency frequency syndrome and/or urgency incontinence, b) chronic urinary retention, and c) combination of urgency frequency syndrome and/or urgency incontinence and chronic urinary retention. After a 2 months SNM optimization phase following neuromodulator implantation, the neuromodulator is turned ON or OFF in a 1:1 allocation by an investigator not involved in the assessment of the clinical outcome.The Figure 
1 gives an overview of the procedures that the patients will undergo during the course of the study.

**Figure 1 F1:**
[figure not shown]
**Flowchart of the sacral neuromodulation (SNM) trial.** SNM: sacral neuromodulation.

### Study population and recruitment

According to the inclusion and exclusion criteria (Table 
1), we will investigate patients with refractory neurogenic LUTD. The following variables will be considered: gender, age, neurological disease, duration of neurological disease, previous treatment, bladder diary variables, urinalysis, urethro-cystoscopy, bladder washing cytology, urodynamic investigations, and questionnaires, i.e. Female Sexual Function Index (FSFI)
[10]/International Index of Erectile Function (IIEF)
[11] and Qualiveen
[12].

**Table 1 T1:** Inclusion and exclusion criteria for patients with refractory neurogenic lower urinary tract dysfunction (LUTD)

**Inclusion criteria**	**Exclusion criteria**
▪ Age >18 years	▪ Age <18 years
▪ Refractory neurogenic LUTD	▪ Non-neurogenic LUTD
▪ Urgency frequency syndrome and/or urgency incontinence refractory to antimuscarinics (pharmacotherapy for at least 4 weeks with at least 2 antimuscarinics)	▪ Botulinum toxin injections into the detrusor and/or urethral sphincter in the last 6 months
▪ Chronic urinary retention refractory to alpha-blocker (pharmacotherapy with an alpha-blocker for at least 4 weeks)	▪ Pregnancy or breast feeding
▪ Combination of urgency frequency syndrome and/or urgency incontinence refractory to antimuscarinics (pharmacotherapy for at least 4 weeks with at least 2 antimuscarinics) and chronic urinary retention refractory to alpha-blocker (pharmacotherapy with an alpha-blocker for at least 4 weeks)	▪ Individuals especially in need of protection (according to Research with Human Subjects published by the Swiss Academy of Medical Sciences ( http://www.samw.ch/en/News/News.html))
▪ Written informed consent	▪ No written informed consent

### Determination of sample size

We are planning a study of independent cases and controls with 1 control per case. Prior data indicate that the (spontaneous) success rate among controls is 0.15. If the true success rate for experimental subjects (SNM ON) is at least 0.5, we will need to study 27 experimental subjects (SNM ON) and 27 control subjects (SNM OFF) to be able to reject the null hypothesis that the failure rates for experimental (SNM ON) and control subjects (SNM OFF) are equal with probability (power) 0.8. The type I error probability associated with this test of this null hypothesis is 0.05. Taking into account potential drop-outs, we will include 30 patients per group.

### Investigations

In case the patients with refractory neurogenic LUTD fulfill the study inclusion criteria following neuro-urological evaluation (bladder diary for at least 3 days, urinalysis, urodynamic investigation, urethro-cystoscopy and bladder washing cystology, Qualiveen questionnaire
[12], FSFI
[10]/IIEF
[11], they are included after providing written informed consent. The Figure 
1 gives an overview of the procedures that the patients will undergo during the course of the study. After minimally invasive bilateral tined lead placement into the sacral foramina S3 and/or S4 (stage one), patients undergo prolonged SNM testing for 3–6 weeks completing a bladder diary to assess the response to treatment. In accordance with the literature
[5,6], an improvement of at least 50% in the key bladder diary variables (i.e. number of voids and/or number of leakages, post void residual) compared to the baseline values is considered a positive test and an indication for neuromodulator implantation. At the end of the test phase, the patients have a neuro-urological re-evaluation (bladder diary for at least 3 days, urinalysis, urodynamic investigation, Qualiveen questionnaire
[12], FSFI
[10]/IIEF
[11]). In case of negative prolonged SNM testing, the tined leads are explanted. In case of successful prolonged SNM testing, the neuromodulator is generally implanted in the upper buttock (rarely in the anterior abdominal wall) (stage two). After neuromodulator implantation, each patient has a 2 months phase when the neuromodulator is turned ON using sub-sensory threshold stimulation (SNM optimization phase) to optimize the effectiveness of neuromodulation by determining the most effective stimulation parameters (choice of stimulation electrodes, intensity of stimulation) for each patient. At the end of the SNM optimization phase, patients are randomized in a double-blind parallel design to SNM ON or OFF. During an outpatient visit, neuromodulation parameters and bladder diary parameters are checked and the neuromodulator is turned ON or OFF by an investigator not involved in assessment of the clinical outcome. Considering that sub-sensory stimulation is used for SNM, the patients do not feel if the stimulation is ON or OFF. At the end of the 2 months double-blind SNM phase, the patients have a neuro-urological re-evaluation (bladder diary for at least 3 days, urinalysis, urodynamic investigation, Qualiveen questionnaire
[12], FSFI
[10]/IIEF
[11]). During this visit, unblinding takes place and the neuromodulator is turned ON in all patients.

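### The diary check at the switching visit has no stated role in the strata or the primary comparison, so precision from a plausibly strong pre-randomisation predictor is missed

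*Protocol article*

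**What the plan says.** All places are in the protocol article.

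- **Response requirement.** Under Investigations, the one stated response requirement is the test phase of 3–6 weeks before implantation, with improvement of at least 50% in the key diary variables.
- **Run-in.** After implantation every patient has 2 months ON at sub-sensory threshold, while electrodes and intensity are tuned. Then: "At the end of the SNM optimization phase, patients are randomized in a double-blind parallel design to SNM ON or OFF".
- **Switching visit.** "During an outpatient visit, neuromodulation parameters and bladder diary parameters are checked and the neuromodulator is turned ON or OFF". No threshold, stratum or analysis is attached to this check.
- **Strata.** Under Study design, "patients are randomized using a computer program considering 3 strata according to the neuro-urological diagnosis".
- **Analysis.** Univariate analysis names chi-squared tests for dichotomous variables. Multivariate analysis adds logistic regression to adjust for imbalance in baseline parameters and names no covariates.
- **Primary outcome.** Under Study outcome measures, success is at least 50% improvement over baseline, by a rule that depends on the diagnosis.
- **Sample size.** "Prior data indicate that the (spontaneous) success rate among controls is 0.15". The ON arm is planned at 0.50, which gives 27 evaluable patients per arm, raised to 30 for drop-outs.

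**The concern.** Every randomised patient has passed the 50% test, yet the planned success rate under ON is only 0.50 by the same 50% criterion. So the plan itself expects about half of the test responders not to be successes at the end of the blinded phase, even with stimulation kept on. Some of them may already be visible at the switching visit. That visit follows 2 months at tuned settings, which are presumably the settings the ON arm continues. A patient who is not a success then is likely to fail in either arm and says little about ON against OFF.

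With about 27 per arm, the share of current responders will differ between arms by chance. An unadjusted test treats that difference as noise; a test stratified by visit status removes it. The baseline adjustment in Multivariate analysis does not clearly reach this variable. Baseline elsewhere in the article is the value from which improvement is measured, recorded before the leads are placed.

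What is at stake is precision and ease of interpretation in a small trial whose patients have had two operations. Validity is not at stake.

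**Working it through.** **1. Inputs from the article (Determination of sample size).** Success 0.15 (OFF) and 0.50 (ON), type I error 0.05, power 0.8, 27 evaluable per arm. Sidedness is not stated.

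**2. The plan's own figure.** Pooled-variance formula, two-sided, no continuity correction, mean rate 0.325:

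n = [1.96·√(2·0.325·0.675) + 0.842·√(0.50·0.50 + 0.15·0.85)]² / 0.35² = (1.298 + 0.517)² / 0.1225 ≈ 26.9, so 27 per arm.

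This matches. Power at 27 is 0.80 by the formula and 0.82 by exact enumeration of the uncorrected chi-squared test. The value 0.82 is the reference below.

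**3. Chance imbalance in visit responders.** Let s be the share of responders at the visit (assumed; the article gives none). The difference in share between arms has SD = √(2s(1−s)/27). At 27 per arm, more than 15 points means at least 5 patients (4/27 = 14.8%, 5/27 = 18.5%). The last column is simulated.

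| s | SD, points | Difference above 15 points |
|---|---|---|
| 0.60 | 13.3 | about 21% of trials |
| 0.70 | 12.5 | about 18% |
| 0.80 | 10.9 | about 12% |
| 0.90 | 8.2 | about 4% |

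**4. Power with and without the factor.** Simulation of 40,000 trials, 27 per arm: uncorrected chi-squared test against a Mantel-Haenszel test stratified by visit status. The success rates by visit status are assumptions, chosen so that the overall rates stay at the planned 0.50 and 0.15. For example, with s = 0.70: ON 0.7·0.68 + 0.3·0.08 = 0.50; OFF 0.7·0.20 + 0.3·0.033 = 0.15.

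| Assumed situation | ON: responder / non-responder | OFF: responder / non-responder | Unadjusted | Stratified |
|---|---|---|---|---|
| 60% responders, strong predictor | 0.78 / 0.08 | 0.22 / 0.045 | 0.82 | 0.89 |
| 70%, strong | 0.68 / 0.08 | 0.20 / 0.033 | 0.82 | 0.87 |
| 80%, strong | 0.60 / 0.10 | 0.18 / 0.03 | 0.82 | 0.84 |
| 90% | 0.54 / 0.14 | 0.16 / 0.06 | 0.82 | 0.82 |
| 70%, moderate | 0.60 / 0.27 | 0.18 / 0.08 | 0.82 | 0.82 |
| 70%, weak | 0.55 / 0.38 | 0.16 / 0.13 | 0.82 | 0.81 |
| Status predicts nothing | 0.50 / 0.50 | 0.15 / 0.15 | 0.82 | 0.80 |

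Repeat runs agree to within about one point.

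**5. Type I error.** With no effect of ON against OFF, the stratified test rejects in about 5% of trials, so the gain is not bought with false positives.

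**The case against.** The strongest objection is that this is ordinary analysis-plan content. Logistic regression is already planned, its covariates are unnamed, and nothing excludes the visit diary. That stands in part: an analysis plan that is not shown may cover it. But the article does fix the strata, names an unadjusted test and ties adjustment to baseline, and none of these brings in the status at the switching visit.

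A second objection is that the gain depends on inputs the documents do not supply. That stands in full. With few non-responders or a moderate predictor the gain is nil, and with an uninformative one there is a small loss.

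Two stronger readings are tempting and are not supported:

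- **That the check serves no purpose.** The article states no statistical use. But checking diary and settings together at the end of a tuning phase fits that phase's stated aim.
- **That randomising current non-responders dilutes the effect and costs planned power.** This would follow only if 0.50 and 0.15 described visit responders alone. With assumed non-responder shares of 10–30% and equal success in both arms among them (0.15 or 0), the difference shrinks to 0.35·(1 − share), and power at 27 per arm falls to between 73% and 53%. The article does not say so. A planned 0.50 among patients who all passed the 50% test may well allow for lost response already. If 0.50 and 0.15 are the rates in everyone randomised, no planned power is lost.

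Nor is there bias. Comparing all randomised patients estimates the effect in implanted test responders, and the diagnosis strata are sensible because the outcome rule differs by diagnosis.

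**Conclusion.** The point holds as a cheap improvement in precision. The article describes a diary check just before the switch and gives it no stated role in stratification or in the primary comparison. At 27 per arm and overall rates of 0.50 and 0.15, using it would change power from 0.82 to between about 0.80 and 0.89. The upper end needs about 60% responders at the visit and a strong predictor; the lower end applies if visit status is unrelated to outcome. The responder share and the success rates by visit status are assumptions throughout. A possible gain of up to 7 points against a possible loss of about 2 favours including the factor, since status under the same stimulation is likely to be informative.

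**What to change.** 1. Confirm that the diary at the switching visit is recorded well enough to score. The article asks for at least 3 days at the other evaluations but gives no length for this one.
2. From that diary, derive improvement of at least 50% over baseline (yes/no) by the rule under Study outcome measures. Record and score it before unblinding.
3. Pre-state this variable as a factor in the primary ON–OFF comparison, for example by a Mantel-Haenszel test or logistic regression, with all randomised patients kept.
4. Pre-state ON against OFF among visit responders as a supporting result.
5. State what the check is for, and which population the planned 0.50 describes.

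The cost is one derived variable, a sentence or two in the analysis section, and attention to diary completeness at a visit that already takes place. The downside is about 2 points of power if visit status does not predict outcome. No patient, visit or clinical rule changes, and no position is taken on who should be randomised.

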### Safety

The investigators will inform the patients, the study monitoring board, and the ethics committee if it becomes evident that the disadvantages of participation may be significantly greater than was foreseen in the research proposal. The study will be suspended pending further review by the study monitoring board, except insofar as suspension would jeopardize the patients’ health. The investigators will take care that all patients are kept informed.

Adverse events will be assessed and categorized according to the National Cancer Institute Common Terminology Criteria for Adverse Events (CTCAE) version 4 in grade 1 to 5 (
http://ctep.cancer.gov/protocolDevelopment/electronic_applications/ctc.htm). All adverse events will be followed until they have abated, or until a stable situation has been reached. Depending on the event, follow-up may require additional tests or medical procedures as indicated, and/or referral to the general physician or a medical specialist.

In the case of withdrawal of consent to participate in the study, all possible efforts will be made to convince the patient to continue to have safety follow-up evaluations.

In the event one of the following situations arises among treated patients during the conduct of the study, the study will be temporarily suspended and a comprehensive safety review conducted evaluating if the study has to be terminated prematurely:

▪ Any death secondary to rapid unexpected progression of an underlying medical condition.

▪ Severe clinical or neurological deterioration in more than one subject.

▪ Any other serious adverse event determined by the study monitoring board to be a reason to suspend the study.

### Study outcome measures

Primary: Success of SNM: Defined in accordance with the literature
[5,6] as improvement of at least 50% in the key bladder diary variables (i.e. number of voids and/or number of leakages, post void residual) compared to the baseline values (i.e. patients with urgency frequency syndrome and/or urgency incontinence: at least 50% decrease in number of voids and/or number of leakages; patients with chronic urinary retention: at least 50% decrease in post void residual; patients with a combination of urgency frequency syndrome and/or urgency incontinence and chronic urinary retention: at least 50% decrease in number of voids and/or number of leakages, and/or at least 50% decrease in post void residual).

Secondary: A) Adverse events: Categorization according to the National Cancer Institute Common Terminology Criteria for Adverse Events (CTCAE) version 4 in grade 1 to 5 (
http://ctep.cancer.gov/protocolDevelopment/electronic_applications/ctc.htm).

B) Urodynamic parameters: cystometric capacity (mL), compliance (mL/cmH_2_O), detrusor overactivity (if yes: bladder volume (mL) at detrusor overactivity, maximum detrusor pressure amplitude (cmH_2_O), detrusor leak point pressure (cmH_2_O)), maximum detrusor pressure (cmH_2_O), detrusor pressure at maximum flow rate (cmH_2_O), maximum flow rate (mL/s), voided volume (mL), post void residual (mL), pelvic floor electromyographic activity (normal/detrusor sphincter dyssynergia).

C) Questionnaires, i.e. Qualiveen and FSFI/IIEF.

D) Costs of SNM.

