#### Univariate analysis

T-tests will be used to compare means between groups and chi-squared tests to compare dichotomous variables.

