#### Multivariate analysis

To adjust for unequal distribution of parameters at baseline, multivariate regression models, linear models in case of an interval scaled outcome and logistic regression in case of a dichotomous outcome will be performed.

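### Three urodynamic parameters have values only in patients with detrusor overactivity at follow-up, so t-testing them compares subsets selected after randomisation

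*Protocol article*

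**What the plan says.** Under Study outcome measures, secondary outcome B lists "detrusor overactivity (if yes: bladder volume (mL) at detrusor overactivity, maximum detrusor pressure amplitude", with detrusor leak point pressure closing the same parenthesis. Overactivity itself (present or absent), cystometric capacity, compliance and maximum detrusor pressure stand outside the condition.

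The section Investigations places the outcome measurement after the randomised phase: "At the end of the 2 months double-blind SNM phase, the patients have a neuro-urological re-evaluation (bladder diary for at least 3 days, urinalysis, urodynamic". The quote breaks off inside the list, which also names the questionnaires. Allocation precedes it, since "the neuromodulator is turned ON or OFF in a 1:1 allocation" at the end of the optimisation phase (Study design).

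For the comparison, Univariate analysis states: "T-tests will be used to compare means between groups and chi-squared tests to compare dichotomous variables". Multivariate analysis adds regression with a stated purpose: "To adjust for unequal distribution of parameters at baseline, multivariate regression models". The article assigns no value or rank, on the three conditional parameters, to a patient without overactivity.

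**The concern.** Whether a patient has overactivity after two months of ON or OFF is an outcome of the trial, not a baseline trait. A patient in the ON group whose overactivity has disappeared has the best result available on this parameter, yet has no pressure amplitude, no volume at overactivity and no leak point pressure to enter into a mean. The patients left in each group are then those who kept overactivity under their own treatment, and randomisation no longer makes them comparable. Adjusting for baseline imbalance is not designed to repair selection that happens after allocation.

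At stake is how three secondary parameters, two of them bladder pressures, are read. A benefit could be reported as no difference, or as higher pressure under stimulation.

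**Working it through.** **The plan's own figure.** The protocol gives no figure for the urodynamic outcomes. Its only calculation is for the primary outcome: success 0.15 OFF and 0.50 ON, power 0.80, type I error 0.05. Two-sided, with pooled variance and no continuity correction:

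n = [1.960·√(2·0.325·0.675) + 0.842·√(0.5·0.5 + 0.15·0.85)]² / 0.35² = (1.298 + 0.517)² / 0.1225 = 26.9, so 27 per group.

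This reproduces the stated 27. It does not bear on the point; I use it only as the group size below.

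**Assumed inputs.** The documents give no overactivity rates and no pressure distributions. All pressures and rates below are my assumptions, chosen to show how the mechanism works.

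**Model 1: amplitude X without stimulation is lognormal, mean 40, SD 25 cmH2O.** Then σ² = ln(1 + (25/40)²) = 0.330, σ = 0.574, μ = ln 40 − σ²/2 = 3.524. The mean above a cut-off c is

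E[X | X > c] = 40·Φ(d + σ)/Φ(d), with d = (μ − ln c)/σ.

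*Scenario A.* ON lowers every amplitude by 15, and overactivity is recorded only above 15.
- Overactivity present: P(X > 15) = 92% OFF; P(X > 30) = 58% ON.
- Mean among those with overactivity: 42.4 OFF; 53.7 − 15 = 38.7 ON.
- Apparent reduction: 42.4 − 38.7 = 3.7 cmH2O instead of 15.

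*Scenario B.* ON abolishes overactivity in the mildest 30% and leaves everyone else unchanged.
- The 30th percentile is 25.1; the mean above it is 49.4, against 40 in OFF.
- Apparent excess in ON: 9.4 cmH2O, although no patient's amplitude rose.

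Simulated trials with 27 per group (20,000 per scenario, two-sided 5% tests, chi-squared without correction):

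| Test | Scenario A | Scenario B |
|---|---|---|
| t-test among patients with overactivity | significant in about 7% | significantly worse for ON in about 26% |
| Rank test, all patients, no overactivity ranked best | about 76% | about 9% |
| Chi-squared on overactivity yes/no, all patients | about 88% | about 98% |

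**Model 2, a check with different assumptions.** Amplitude is normal, mean 40, SD 20. Overactivity persists in 80% of OFF and a proportion p of ON. The correlation between severity and persistence is ρ. ON truly lowers every amplitude by 5. The apparent ON minus OFF difference is

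−5 + 20ρ·[λ(p) − λ(0.80)], with λ(p) = φ(z_p)/p, z_p the standard normal quantile of p, λ(0.80) = 0.350, λ(0.50) = 0.798, λ(0.35) = 1.058.

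- ρ = 0, any p: −5.0, no bias.
- ρ = 0.5, p = 0.50: −5 + 10·0.448 = −0.5.
- ρ = 0.5, p = 0.35: −5 + 10·0.708 = +2.1.
- ρ = 0.8, p = 0.35: −5 + 16·0.708 = +6.3.

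Of 27 per group, 27·0.80 = 21.6 OFF patients would enter the comparison, and between 27·0.35 = 9.5 and 27·0.70 = 18.9 ON patients for p from 0.35 to 0.70.

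**The case against.** The strongest reply is that the outcome section is a measurement list and the statistics section a single generic sentence. Neither says in so many words that the conditional values will be t-tested among patients still overactive, and an analysis plan not shown here may handle them. That is fair as to certainty, and it limits the point to what follows if the published rule is applied as written. It does not remove the point: the article names these parameters as secondary outcomes and states one test for means, and together these condition on a post-randomisation state.

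Second, the plan already contains sound comparisons. Overactivity yes/no is an outcome with a planned chi-squared test, which in the two scenarios above has about 88% and 98% power. Cystometric capacity and maximum detrusor pressure are listed for all patients. This stands. A reader might infer that the urodynamic results as a whole would miss or invert a benefit; the documents do not support that.

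Third, a reader might extend the point to maximum flow rate and voided volume in patients who cannot void. The outcome section puts no condition on those variables and nothing says such patients are left out, so the extension has no basis in the text.

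Fourth, the bias is not inevitable. With persistence unrelated to severity it is zero. Every patient in Model 1 also starts with a positive amplitude, whereas one of the trial's three strata is chronic urinary retention, where overactivity may be absent from the start.

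**Conclusion.** The point holds for bladder volume at overactivity, maximum detrusor pressure amplitude and detrusor leak point pressure. Followed as written, the plan compares their means between subsets that treatment may have selected.

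The size cannot be fixed from the documents. Under assumed inputs a true 15 cmH2O reduction appears as about 4, an excess of about 9 cmH2O appears in ON where no amplitude rose, and a true 5 cmH2O reduction ranges from fully preserved to reversed (+6.3). These distortions require that overactivity is lost preferentially in milder patients; it would be wrong to say that the comparison is biased in every case. Where that condition holds, a larger sample does not remove the bias.

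The primary outcome, the sample size and the unconditional urodynamic parameters are not touched. It is worth correcting because a misleading pressure result is avoided by wording alone.

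**What to change.** - Name overactivity yes/no at the end of the blinded phase, in all randomised patients, as the main comparison for this parameter, using the chi-squared test already planned.
- If amplitude or volume at overactivity is to be tested, include all randomised patients and use a rank-based composite in which absence of overactivity ranks best.
- Report the values among patients with overactivity, including leak point pressure, by group as description only, with the number contributing and no between-group test.

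No new data, visits or patients are needed. The price is that a rank summary replaces the mean difference, and the composite answers a broader question than amplitude alone. It can also have low power when only mild overactivity is abolished (about 9% in Scenario B), which is why the yes/no comparison should lead.
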